### Attrition and adherence

Attrition will be considered under the following conditions: a) two consecutive or three alternate absences during treatment sessions; b) inability to complete the post-test and follow-up; c) development of any disabling condition for participation in the study. Regarding adherence strategies, up to two non-consecutive absences can be compensated the following week. There will also be flexible hours offered for receiving therapy, as well as direct contact by telephone with participants confirming the evaluation dates and reinforcing treatment adherence [33]. Additional measures to prevent dropouts will also be applied, such as periodic evaluations (during the outcome analyses) on satisfaction with therapy, discussion of difficulties in continuing with treatment (for example, transport logistics to the laboratory), and attempts to resolve and prevent possible problems that may interfere with adherence and continued participation in the study.

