### Randomization and blinding

The method of randomization will be a 1:1 permuted block randomization generated by a web-based randomization tool (www.random.org). This sequence will be done independently and remotely by a blinded investigator who will not have contact with other research procedures. The randomization will be concealed until group allocation.

After the randomization process, a blind researcher not involved with the recruitment, data collection, or intervention will perform the allocation of participants between the groups. This will be employed by concealed allocation of sequentially numbered, opaque, sealed envelopes, so that the person responsible for allocation will not have contact with patients or with the work of others. This envelope will be delivered one day before the treatment sessions to the researcher responsible for neurostimulation, who will not be involved with the other procedures for collection or data analysis.

Participants will not be identified by their real names and will not be aware of which arm of the study they are allocated to. When included in the study, they will receive a sealed, opaque envelope containing their respective identification code. In this way, the assessors will also be blind, as they will be identifying the patients by codes and will not have contact with other research procedures. The same will happen to the staff responsible for the execution of CIMT procedures. Data analysis will be conducted by a researcher not involved in any stage of recruitment, screening, assessment, or intervention.

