### Data analyses

The design of the statistical analysis is based on previous studies of literature relating to clinical and placebo-controlled trials using tDCS [17, 30, 90, 91]. The intention-to-treat analysis will be used; however, high or differential rates of missing data between treatment arms/sides may indicate a departure from this assumption and may lead to bias [92]. Thus, a sensitivity analysis will be performed with different allocation procedures to verify the strength of the data. The best strategy resulting from the comparison of the following methods will be chosen: last observation carried forward, complete case analysis, likelihood-based methods, and multiple imputation [93]. As pointed out by White et al. [94] in the intention-to-treat analysis strategy, the main focus in the analysis of choice should be the plausibility of its assumptions, while the inclusion of all randomized individuals is a requirement only for sensitivity analysis.

Multivariate imputation by chained equations (MICE, the R Foundation for Statistical Computing, Vienna, Austria) and SPSS Ver.20.0 (SPSS Inc., Chicago, IL, USA) software will be used.

Regarding sociodemographic and clinical characteristics at the baseline, for continuous variables, information on the variability will be presented for example, mean and standard deviation). If groups are similar to each other, descriptive data analysis will be performed. However, if important differences are found, regression analysis will be used to evaluate these data to estimate the effects of covariates with the variables of interest.

Regarding clinical outcomes, the primary outcome will be analyzed with analysis of mean change scores (MCS) to the total score of BI. The MCS will be evaluated in three ways: change occurred between the post and pre-test (T1-T0); between endpoint and pre-test (T2-T0); between the endpoint and post-test (T2-T1). The baseline as covariate will be used to identify potential differences between the groups by analysis of covariance (ANCOVA) [95].

Finally, the effect sizes and confidence intervals of change scores will be calculated using Cohen’s *d*, using the Hedges correction, with values of 0.20, 0.50, and 0.80, reflecting small, medium, and large effects, respectively [96]. For all variables of the secondary outcomes, the same analysis strategy will be used. Non-parametric tests will be performed if some of the outcomes do not meet the conditions necessary for parametric analysis.

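### Attrition is defined partly by missed sessions, which lets patients with a measurable Barthel index be dropped or imputed under an intention-to-treat label

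*Protocol article*

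**What the plan says.** The section on attrition and adherence gives three conditions for attrition. The first concerns attendance: "Attrition will be considered under the following conditions: a) two consecutive or three alternate absences during treatment sessions". The second concerns the outcome visits: "b) inability to complete the post-test and follow-up". The third is a disabling condition that prevents participation. The same section allows limited make-up sessions ("up to two non-consecutive absences can be compensated the following week") and presents its other measures as ways to prevent dropout and keep patients in the study.

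The Data analyses section says: "The intention-to-treat analysis will be used; however, high or differential rates of missing data between treatment arms/sides may indicate a departure from this assumption". It then plans a comparison of methods: "The best strategy resulting from the comparison of the following methods will be chosen: last observation carried forward, complete case analysis", with likelihood-based methods and multiple imputation as the other two candidates. Citing a published strategy for intention-to-treat analysis, it adds that "the inclusion of all randomized individuals is a requirement only for sensitivity analysis".

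The Sample size section raises the number per group from 12 to 20 to cover loss. It names three kinds of loss: withdrawal, being unable to carry on with treatment, and death.

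**The concern.** Missing treatment sessions and missing outcome data are different events. The first is non-adherence after randomisation, and the patient can still attend T1 and T2. The second leaves a gap that some method has to fill. The article puts both under one label and attaches to that label a missing-data plan that includes complete case analysis.

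If the absence rule were applied as loss from the study, a patient who missed two sessions in a row could be left out, or given an imputed value in place of one that could have been observed. The comparison would then lean towards patients who attended. Attendance may be informative. The limitations section expects absences from transport problems and personal difficulties, and these could track the function that the Barthel index measures. Discomfort under active current could also make absence differ by arm. The article does not show that either happens. With 20 patients per arm, each exclusion carries weight.

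**Working it through.** **What the absence condition adds.** Patients who cannot complete the outcome visits are already covered by the second condition, and patients with a disabling condition by the third. The absence condition therefore changes the status only of patients who meet neither, and these are the patients who could still be assessed at T1 and T2.

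**What can then happen to them in the analysis.**
- Under complete case analysis they are left out, if no outcome is recorded or used.
- Under last observation carried forward, sessions run between T0 and T1. If assessment ends with attrition, the only value is the T0 score, and the changes T1-T0 and T2-T0 are both entered as zero.
- Under likelihood-based methods or multiple imputation they stay in, but with a modelled value where an observed one was possible.
- The requirement to include all randomised patients is attached only to the sensitivity analysis, so it does not protect the primary analysis.

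**Is power the problem?** Inputs from the Sample size section: difference 10, SD 7, alpha 0.05 (two-sided assumed), power 90%. The two-sample t-test gives 11.35, so 12 per group, which reproduces the article's figure. Power is 91.7% at 12 and 99.3% at 20 per group. Going from 12 to 20 absorbs a loss of 1 - 12/20 = 40%. Power is not the issue; possible selection after randomisation is.

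**How many patients could meet the rule?** The article gives no absence rate. Assume 10 sessions and independent absences with probability p, and read three alternate absences as any three. A patient avoids the rule with no absence, one absence, or two that are not adjacent. There are 45 - 9 = 36 non-adjacent pairs, so

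P(rule met) = 1 - [(1-p)^10 + 10p(1-p)^9 + 36p²(1-p)^8].

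| p (assumed) | P(rule met) | Expected of 40 |
|---|---|---|
| 2% | 0.4% | 0.2 |
| 5% | 2.6% | 1.1 |
| 10% | 10.9% | 4.4 |
| 15% | 23.5% | 9.4 |

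**How large could the bias be?** If the patients who meet the rule are left out, the bias in the difference is (share removed x shortfall) in the active arm minus the same product in the sham arm. Assume 3 of 20 active and no sham patients, with change 10 points below the other 17, whose mean change is m:
- mean of all 20 = (17m + 3(m - 10))/20 = m - 1.5
- mean of the 17 = m
- shift = 1.5 points, which is 15% of the planned 10.

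The standard error of the difference at 20 per arm is 7 x √(2/20) = 2.2, so the shift is 1.5/2.2, or about 0.7 standard errors. With equal shares and shortfalls in both arms the two products cancel and the bias is zero.

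Last observation carried forward can push the other way. If 3 of 20 active patients in fact improved by 10 points and were entered as zero, the active mean would fall by 3 x 10/20 = 1.5 points.

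**The case against.** A reader might infer that the rule removes randomised patients and contradicts the intention-to-treat statement. The documents do not support that. No sentence says that patients who meet the absence condition are withdrawn, go unassessed, have scores discarded or leave the analysis. Attrition may be only a reporting category. Two of the four candidate methods keep patients with incomplete outcomes, and the sentence about sensitivity analysis concerns missing data and does not mention absences. All of this stands.

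It also stands that a link between absence and arm is only a possibility. Patients are blinded, and both arms have the same visits and the same 3-hour therapy. The 1.5-point figure is correct arithmetic on deliberately unfavourable assumed inputs; at a 5% absence rate only about one patient of 40 would meet the rule.

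A further argument is that a condensed article may leave follow-up of non-adherent patients and analysis sets to a full protocol or analysis plan. This carries less weight. The point does not rest on silence: the article itself states an attrition rule that includes missed sessions, counts inability to continue treatment as loss, and sets out a missing-data plan under which those patients may be left out of the primary analysis. A fuller document could settle the matter, but these passages would still need to agree with it.

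**Conclusion.** The concern holds as a permission, not as a contradiction. As written, the plan allows patients to be dropped or imputed for non-adherence although their Barthel index could be observed. Applied that way, the analysis would not be intention-to-treat.

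The size of any bias cannot be derived from the article. It depends on how many patients met the rule, in which arm, how their change differed, and which method is chosen. The illustrations run from zero (balanced arms) to 1.5 points in either direction (3 of 20 active patients, none in sham). Power is not threatened. This should be fixed before the final analysis, but it does not by itself invalidate the design.

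**What to change.** - Define the absence condition as non-adherence, and reserve attrition for outcomes actually not obtained.
- State that non-adherent patients keep the T1 and T2 assessments already scheduled.
- Analyse every Barthel value collected, in the randomised arm, whatever the attendance.
- Apply the missing-data methods only to values that were not obtained.
- Report the number of sessions received by arm, and the number of patients meeting the absence condition.
- Bring the list of losses in the Sample size section into line.

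The Trial status section reports 40 patients randomised by the end of December 2015, so the main change is to the analysis rule, to be recorded before the data are analysed by arm. The cost is a few sentences, plus any scheduled visits still to come. No treatment or attendance rule for patients needs to change.

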### Safety

With regards to adverse effects, patients will be asked at every stimulation session about the effects experienced such as “tingling,” “burning,” “headache,” “sleepiness,” and others, which they will then score in intensity (1 - no, 2 - mild, 3 - moderate, 4- strong), and this effect is related to the stimulation in a Likert scale of 1 (no relation) to 5 (strongly related) [33].

Regarding safety, deleterious cognitive effects, that is any effect from therapy detrimental to cognitive functions, will be analyzed using the following neuropsychological tests referenced in the literature: Montreal Cognitive Assessment (MoCA), which assesses cognitive dysfunction [87]; the Victoria version of the Stroop Color and Word Test, to measure executive functions [88]; the Digit Span subtest, which evaluates attention and (direct order) and working memory (indirect order) [89]. A cognitive evaluation will be conducted at the beginning and end of the study to check if there really are deleterious effects of neurostimulation, so that the values at baseline can be used as a reference.

We could find no literature reports of any deleterious cognitive effect after application of tDCS. It is considered a safe technique that has been used for several years in post-stroke patient treatment [9, 22, 33, 81].

If the patient experiences any loss or strong discomfort, the treatment will be stopped and medical care as well as physical and psychological therapy will be offered for control of potential problems and to promote recovery.

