## Methods

### Overview

This is a placebo-controlled, double-blind, randomized clinical trial (Fig. 1), in which 40 patients are divided into two groups of 20 participants each. In Fig. 1, the CONSORT (Consolidated Standards of Reporting Trial) flowchart [32] shows the number and distribution of participants: Group A1 - participants in post-stroke subacute stage that receive active tDCS combined with CIMT; Group A2 - participants in the post-stroke subacute stage who receive a placebo stimulation associated with CIMT. Patients will undergo three assessments: baseline (T0), week 2 (T1), and week 4 (T2). Neuropsychological tests will be performed at T0 and T2. Adverse events will be measured in each session, where the researcher responsible for administering the neurostimulation will question the patient on whether they experience any uncomfortable or painful sensation, and if this is related to the tDCS, following the procedure of Brunoni et al. [33]. At the end of the study, participants who received tDCS and showed clinical improvement will be invited to receive bimonthly stimulation for 12 months as part of a longitudinal study of tDCS for stroke. Those who received the tDCS placebo and did not respond will be invited to receive daily sessions with an active current for 10 days. Finally, those who had a response to the placebo will be referred for other physical therapy treatment.

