### Inclusion criteria

Patients will be selected according to the following inclusion criteria: a) age between 18 and 65 years; b) diagnosis of unilateral, non-recurring, subacute stroke of ischemic and lacunar type, as defined by the International Classification of Diseases (ICD-10) through computed tomography or magnetic resonance imaging conducted by neurologists; c) a score < 1 on the consciousness and communication items of the National Institutes of Health Stroke Scale (NIHSS) [34]; and d) the patient provided written informed consent.

Although the subacute phase of stroke generally comprises the period of 7 to 90 days after injury [35–38], this study will only include those at 1–3 months after stroke to avoid the inclusion of participants in the acute phase. The definition of the age group followed the age interval often found in studies involving tDCS and stroke [17, 39, 40]. However, for a more conservative position of experimental control, we preferred to limit the inclusion up to 65 years of age to avoid this variable possibly interfering in the performance of elderly participants, as this could increase the chances that there are other conditions associated with aging (such as concentration and memory).

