### Exclusion criteria

Patients will be excluded if they have: a) a score between 25–32 points on the NIHSS [34] and grade/degree 5, according to the Rankin scale [41]; b) cognitive deficits (a score below 24 points on the Mini Mental State Examination) [42]; c) an inability to actively carry out wrist flexing/bending, that is, metacarpophalangeal and interphalangeal active extension of 10° to 20° wrist extension.

In addition, exclusion criteria relating to contraindications of neurostimulation will be applied, following the safety guidelines [9, 13]: a) use of psychoactive drugs, as stated in the recommendations; b) patients with implanted metallic or electronic devices; c) cardiac pacemaker; d) seizures; e) acute eczema under the electrodes, the presence of tumors, epilepsy or substance abuse; f) pregnancy (this condition was specifically enlisted as a contraindication in this study as a precaution, as there are no data on maternal and fetal effects of tDCS on pregnant women who have suffered a stroke).

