Regarding safety, deleterious adverse and cognitive effects will be recorded/computed in terms of the proportion in each group, in each time period (T0, T1, and T2), and will be analyzed by the Fisher exact test.

Bias-generating will be tested. The statistical model used for blinding effectiveness was based on the study of Brunoni et al. [97]. The chi-square test or Fisher’s exact test will be used to assess if tDCS blinding guessing was beyond chance for patients, external judges, and trialists. Paired *t*-tests will be used to compare the rate of their guessing according to the Likert scale. Logistic regressions exploring the factors associated with “correct blinding guessing” (that is, participants who correctly guessed their allocation group) will be performed. The factors will be clinical response, high guessing confidence (scores 4 or 5 on the Likert scale), and adverse effects.

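### Continuous cognitive safety scores are reduced to an undefined yes/no count compared by Fisher's exact test, which is insensitive to harm at 20 per arm

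*Protocol article*

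**What the plan says.** All places are in the protocol article.

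- **Overview:** "Neuropsychological tests will be performed at T0 and T2". The neuropsychological battery is therefore given twice, four weeks apart.
- **Safety:** the target is "deleterious cognitive effects, that is any effect from therapy detrimental to cognitive functions", measured by MoCA, the Victoria Stroop test and Digit Span. The battery is repeated "to check if there really are deleterious effects of neurostimulation, so that the values at baseline can be used as a reference".
- **Data analyses, safety paragraph:** "deleterious adverse and cognitive effects will be recorded/computed in terms of the proportion in each group, in each time period (T0, T1, and T2"), and these "will be analyzed by the Fisher exact test".
- **Data analyses, clinical outcomes:** the Barthel index gets mean change scores, ANCOVA with baseline as covariate, and effect sizes with confidence intervals. The same strategy is extended to the secondary outcomes. The secondary list under Outcomes does not include the three cognitive tests.
- **Inclusion criteria:** "this study will only include those at 1–3 months after stroke".

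**The concern.** Three quantitative test scores per patient are collected at two visits and then collapsed into one yes/no state. Nothing says what puts a patient in the yes group: which test, how large a change, or how the tests are combined. A patient on active current who does worse than they would have done on sham, but stays on the unaffected side of the line, adds nothing to the comparison. The efficacy scales in the same trial keep their full information.

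At stake is the safety statement. The Safety section already reports finding no published deleterious cognitive effect and calls the technique safe. A non-significant Fisher test on a handful of cases would readily be read as confirmation, although the test had little chance of finding a moderate harm.

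The timetable is also inconsistent. A proportion with cognitive harm is listed at T0, where no decline from baseline can exist, and at T1, where the battery is not given.

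**Working it through.** **The plan's own figure.** The protocol gives no power for cognitive safety. Its only calculation (Sample size) is for the Barthel index: difference 10, SD 7, 90% power, 12 per group. The normal approximation gives 2 × (7 × (1.960 + 1.282) / 10)² = 10.3, so 11. The exact t-test has 89.0% power at 11 and 91.7% at 12, so 12 reproduces. Enrolment is 20 per group at a 0.05 level, taken here as two-sided.

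**Assumptions, because the documents give no figures.** Change from T0 to T2 is normal with SD 1 in both arms. Sham rises by m and active by m − d, where d is the harm. A case is a fall of more than c below own baseline (c = 0 means any fall). All 20 per arm are analysed.

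**Formulas.**
- Case proportions: p(sham) = Φ(−c − m); p(active) = Φ(−c − m + d).
- Fisher power: the sum of Bin(i; 20, p(active)) × Bin(j; 20, p(sham)) over all pairs (i, j) with two-sided Fisher p ≤ 0.05.
- Mean-change power: noncentral t, 38 df, noncentrality d × √(20/2), critical value 2.024. The noncentrality is 1.58, 2.53 and 3.16 for d = 0.5, 0.8 and 1.0.

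**Results.**

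| Harm d | Rise m | Threshold c | Sham cases | Active cases | Fisher | Mean change |
|---|---|---|---|---|---|---|
| 0.8 | 0 | 0 | 50.0% | 78.8% | 37% | 69% |
| 0.8 | 0.5 | 0 | 30.9% | 61.8% | 37% | 69% |
| 0.8 | 1.0 | 0 | 15.9% | 42.1% | 34% | 69% |
| 1.0 | 0 | 0 | 50.0% | 84.1% | 54% | 87% |
| 1.0 | 0.5 | 0 | 30.9% | 69.1% | 55% | 87% |
| 1.0 | 1.0 | 0 | 15.9% | 50.0% | 54% | 87% |
| 0.8 | 0 | 0.5 | 30.9% | 61.8% | 37% | 69% |
| 0.8 | 1.0 | 0.5 | 6.7% | 24.2% | 22% | 69% |
| 0.8 | 0 | 1.0 | 15.9% | 42.1% | 34% | 69% |
| 0.8 | 1.0 | 1.0 | 2.3% | 11.5% | 5% | 69% |
| 0.5 | 0.5 | 0 | 30.9% | 50.0% | 15% | 34% |
| 0.5 | 1.0 | 0 | 15.9% | 30.9% | 12% | 34% |

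**Where the loss comes from.** If any fall counts, going from no common rise to a rise of 1.0 SD costs about 3 points of power at d = 0.8 and nothing at d = 1.0. The gap to mean change (roughly 32–35 points) is there without any recovery, so it comes from dichotomising. Rise and threshold enter only through their sum, so a common rise hurts once a case also needs a real decline: 37% falls to 22% at c = 0.5, and 34% to 5% at c = 1.0.

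**Counts needed.** With 20 per arm, Fisher reaches p ≤ 0.05 only at 5 against 0, 7 against 1 or 9 against 2 cases.

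**Precision of the alternative.** Without baseline adjustment, the 95% interval for the difference in mean change has half-width 2.024 × √(2/20) = 0.64 SD.

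**The case against.** A reader might infer something stronger: because these patients are recovering and sit the same tests twice, stimulation that slows cognitive recovery would go largely unseen. The documents do not support that.

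- **The sham arm is compared.** Recovery and practice act on both arms. With a 1.0 SD rise, 0.8 SD harm and any fall counted, 58% of active patients still score at or above baseline, but so do 84% on sham. The comparison is insensitive, not blind.
- **Recovery is not the main cause.** Under the any-fall definition it costs 0–3 points of power for rises up to 1.0 SD. It matters with a decline threshold, or with a larger rise (at 1.5 SD: 22% for 0.8 SD harm and 39% for 1.0 SD).
- **Its size is not in the documents.** Excluding patients with "a score below 24 points on the Mini Mental State Examination" may also limit room for gain.

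Two further objections have weight. First, decline against own baseline is an inference. A T0 proportion fits better with a cut-off for impairment at each visit, and scoring rules are often left to a fuller document. That is fair for the missing threshold. It does not excuse the stated choice of a proportion with Fisher's test, or the listing of time points at which the quantity cannot be observed. Second, sample size is a limit under any analysis: at 0.5 SD harm, mean change has only 34% power against 12–15% for the count.

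**Conclusion.** The point holds in limited form. The protocol fixes an inefficient analysis for cognitive safety and leaves the case undefined, while a better method is already in use for its other scales. On the any-fall reading with 20 per arm, the planned test has about half the power of a mean-change comparison at 0.8 SD harm (34–37% against 69%), and 54–55% against 87% at 1.0 SD. A stricter case definition combined with a common rise makes it much worse, down to 22% or 5% at 0.8 SD harm.

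These figures rest on normal change scores with equal SD, no dropout, and assumed values for rise and harm. The inconsistency at T0 and T1 rests on the text alone. This is a safety analysis outside the primary and secondary outcomes and does not touch the Barthel comparison, but it should be corrected because its likely product is a reassuring negative result.

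**What to change.** In the safety paragraph of Data analyses:

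1. Make the cognitive safety comparison the active-minus-sham difference at T2 in each test score (MoCA, Stroop, Digit Span), by ANCOVA with the T0 score as covariate, with a 95% confidence interval.
2. Keep the count of decliners as descriptive, define what counts as a decline, and report it at T2 only.
3. State that the safety conclusion is drawn from the confidence limits, that is, from how large a harm remains compatible with the data, and not from a non-significant test. Add that with 20 per arm power is only about 34% for a 0.5 SD harm, before any gain from baseline adjustment.

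The cost is wording. The scores are already collected at T0 and T2 and the ANCOVA is already planned for the other scales, so no visit, test or patient is added.
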